### 2.8. Statistical Analysis

The Statistical Package for the Social Sciences SPSS (IBM SPSS Statistics, Version 25.0. Armonk, NY, USA) will be used for statistical analyses and computations. Data will be presented as means and standard deviation (SD). The Kolmogorov–Smirnov test and Levene’s test will be applied to check the normality and homogeneity of data. After that, a group × time repeated measures ANOVA will be employed to analyse the impact of the intervention on the various dependent variables. Effect size will also consider Cohen’s d, accompanied by a 95% confidence interval. Statistical significance will be determined for the within-group effect of time and the interaction group × time. Alpha significance level will be established at *p* ≤ 0.05.

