## 2. Materials and Methods

### 2.1. Design

A randomized controlled trial employing a parallel-group design will be implemented, including a 4-week intervention phase. Baseline assessments will be administered prior to commencing the intervention, followed by post-intervention evaluations immediately upon its completion. Participants will be randomly assigned to the experimental or control group. The study will be reported following the SPIRIT Statement and the TIDieR Checklist [28,29].

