### 2.3. Sample Size

An a priori sample size computation was carried out using the G*Power software 3.1.9.4 (Kiel University, Kiel, Germany), selecting the One-way ANOVA statistical test, that allows the comparison between the means of two independent groups to determine whether there will be evidence that the associated population means will differ significantly. Therefore, considering a significance level of 0.05 (alpha), a 0.02 beta risk, and assuming a large effect size f of 0.4, a total of 52 participants (being 26 subjects included in both experimental and control group) will be sufficient in order to attain a minimum power of 80%.

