### 2.7. Measures

PL and body composition will be evaluated through a variety of tools. Prior to conducting the initial measurements, participants will undergo a familiarization phase designed to acquaint them with the various instruments and assessments incorporated within this study.

Socio-demographic data. Participants’ parents or legal guardians will provide socio-demographic data. The informed consent form will be accompanied by a sociodemographic questionnaire which will include age, gender, type of school (public or private), socioeconomic status, other diagnoses, medication, school year, reinforcement at school, and therapies. These data will only be considered at baseline.

The rest of the measures will be taken at baseline and the end of the intervention and will be carried out by the participants (Figure 1).

(1). Physical Literacy. PL level will be assessed using the Canadian Assessment of Physical Literacy (CAPL-2) [43], from which there is also a preliminary validation in adolescents aged 12 to 16 years old [44]. The CAPL-2 employs a numerical scoring system ranging from 0 to 100 points, with 0 representing the lowest possible value and 100 denoting the highest achievable score. This assessment encompasses four distinct domains: (1) daily physical activity behaviour; (2) physical competence; (3) motivation and confidence; and (4) knowledge and understanding. The different domains will be assessed through a combination of concrete tests and assigned a corresponding score, as outlined below:

a. Daily activity behaviour. The total score for this domain will comprise two components: step counts data derived from an activity wristband (Xiaomi mi Band 3, Xiaomi Corporation, Beijing, China) as a feasible and valid alternative to the research-grade accelerometers [45], which will record the number of steps taken over a full week, and a self-reported inquiry concerning the frequency of engaging in at least 60 min of PA per day. Regarding the total score, it will be determined by combining the score derived from the recorded step count and the score attributed to the individual responses on the weekly PA performed.

b. Physical competence. The scores of the following three components will be combined in order to obtain the ultimate score for this domain:

*I. The Plank test* (30) consists of maintaining the plank position for as long as possible. The total time that the participant held this posture will be taken for the evaluation.

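### The group × time ANOVA is an unadjusted change-score test: less precise than a baseline-adjusted analysis, and biased if loss differs between arms and depends on the measured baseline score

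*Protocol article*

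**What the plan says.** Section 2.1 describes a parallel-group trial: "Participants will be randomly assigned to the experimental or control group". Apart from the socio-demographic data, collected once, section 2.7 sets two occasions: "The rest of the measures will be taken at baseline and the end of the intervention". Section 2.8 names SPSS 25 and fixes the effect analysis: "a group × time repeated measures ANOVA will be employed to analyse the impact of the intervention on the various dependent variables". The tests are also named: "Statistical significance will be determined for the within-group effect of time and the interaction group × time". The model as described has group and time as factors and no baseline covariate.

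Section 2.3 plans 26 children per arm from a one-way ANOVA with f = 0.4. Sections 2.3 and 2.8 give no dropout rate and no baseline–post correlation.

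**The concern.** With two occasions, the interaction test is a two-sample t test on each child's change. This has two consequences.

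First, precision. In a randomised trial the baseline differs between arms only by chance. Subtracting it in full carries baseline noise into the estimate unless ρ is close to 1; adjusting for it uses the same data better.

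Second, bias under loss. A child without a post-test has no change score, so the conventional ANOVA leaves that child out. Children selected on a high or low baseline score tend to regress toward the mean. If the two arms lose different parts of the baseline distribution, their remaining children regress by different amounts, and the difference enters the group × time estimate even when the programme does nothing. Uneven loss is plausible here: only the experimental arm has eight after-school sessions to attend (section 2.6, two per week for four weeks), while controls carry on as usual.

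On the ADHD symptom test, where higher is worse, losing the most severe programme-arm children pushes the estimate against the programme. Losing the mildest pushes it in favour.

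**Working it through.** **Inputs from the article.** 26 per arm, alpha 0.05, f = 0.4, so d = 2 × 0.4 = 0.8 (section 2.3); two assessments (sections 2.1 and 2.7); interaction test (section 2.8).

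**Assumed, because the article does not give them.** Equal SD at both visits, set to 1; ρ of 0.5 to 0.7; loss of 20–30% in one arm only.

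**1. The plan's own figure.** An exact F test for two groups with f = 0.4 and 80% power needs 51.05 children, hence 52 in equal arms; power at 52 is 80.7%. The planned 52 reproduces with a beta of 0.20. (Section 2.3 also prints a beta of 0.02. That is a separate inconsistency and is not used here.)

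**2. Precision with no loss.** For n per arm:
- change score: variance = (2/n) × 2(1 − ρ)
- baseline-adjusted: variance = (2/n) × (1 − ρ²)
- ratio, adjusted to change = (1 − ρ²) / [2(1 − ρ)] = (1 + ρ)/2

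With n = 26, 2/n = 0.0769. At ρ = 0.5 the ratio is 0.75, and the SEs are √(0.0769 × 1) = 0.277 and √(0.0769 × 0.75) = 0.240. At ρ = 0.7 the ratio is 0.85, so the gain is 15%.

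**3. Bias when loss depends on the measured baseline.** With no true effect, expected change given baseline x is (ρ − 1)x. The bias is therefore (ρ − 1) × Δ, where Δ is the difference between arms in completers' mean baseline. If the programme arm loses exactly the top fraction p of the baseline distribution, Δ = −φ(z)/(1 − p), with z the cut-off:
- p = 0.20: Δ = −0.280/0.80 = −0.350
- p = 0.30: Δ = −0.348/0.70 = −0.497

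For softer loss, with the odds of leaving multiplied by 4 or by 2 per baseline SD, Δ was obtained by numerical integration.

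| One-arm loss | Δ | Bias, ρ = 0.5 | Bias, ρ = 0.7 |
|---|---|---|---|
| 20%, sharp cut | −0.350 | 0.175 SD | 0.105 SD |
| 30%, sharp cut | −0.497 | 0.248 SD | 0.149 SD |
| 20%, odds ratio 4 | −0.216 | 0.108 SD | 0.065 SD |
| 30%, odds ratio 4 | −0.313 | 0.156 SD | 0.094 SD |
| 20%, odds ratio 2 | −0.129 | 0.064 SD | 0.039 SD |
| 30%, odds ratio 2 | −0.190 | 0.095 SD | 0.057 SD |

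**4. Simulation** (26 per arm, no true effect, 6,000 trials per scenario). Sharp cut at ρ = 0.5: the change-score test is off by 0.17 SD and rejects in 8.6% of trials at 20% loss, and by 0.25 SD and 12.6% at 30%. At ρ = 0.7 it is off by 0.11–0.15 SD and rejects in about 7–9%. Baseline adjustment on the same children gives a bias near 0 and about 5% rejection.

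**5. Controls** (change-score bias, ρ = 0.6). No loss: −0.001 SD. The same baseline-dependent loss in both arms: 0.001 SD. Unequal loss unrelated to baseline: −0.004 SD. Both conditions are needed: loss must depend on baseline and must differ between arms.

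**6. The reverse case.** Suppose one arm loses its most severe children by stable underlying severity, which both visits measure with independent error (ρ = 0.5, sharp cut). Both visit means then shift equally, so the change score is unbiased (−0.003 SD at 20% loss, −0.008 SD at 30%). Adjusting for a noisy baseline removes only part of the shift: the adjusted estimate is off by −0.139 SD and −0.199 SD, rejecting in roughly 8–11% of trials.

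**The case against.** The strongest objection is step 6. The article cannot tell us whether loss would follow the measured score or the child's stable severity. Under the second, the planned ANOVA is unbiased and the adjusted model is off by a similar amount in the opposite direction. This stands. A reader might infer that a mixed model on all randomised children removes the bias outright. It does so only if loss depends on what was measured. Nor does it rescue the comparison by including more children: with complete baselines and loss only at post-test, it gives in effect the same group estimate as ANCOVA on the completers.

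A reader might also infer that the article commits to a completer analysis. It does not say so. Dropping children with one measurement follows from how the named method is usually run, and a full protocol or analysis plan could add imputation. The point therefore rests on the chosen model, not on a missing-data section that an article may leave out.

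A third tempting reading is that the step count, "which will record the number of steps taken over a full week", adds to the bias. Both arms wear the wristband, and equal loss in both arms produces no bias (step 5). The article also does not say that an incomplete week voids the physical literacy score.

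Finally, the sharp-cut figures are an upper case. Softer loss gives roughly 0.04–0.16 SD, against a planned d of 0.8. A shift of that size would not by itself create or hide such an effect. This limits the weight of the point but leaves the precision argument untouched.

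**Conclusion.** The concern holds as a case for a better main model, not as proof that the planned result will be biased. What is certain, given two visits and randomisation, is that the unadjusted change contrast is less precise than a baseline-adjusted one whenever ρ is below 1: 25% more efficient in variance terms at ρ = 0.5 and 15% at ρ = 0.7, assuming equal SDs and no loss. What is conditional is the bias: about 0.1–0.25 SD for 20–30% one-arm loss at the extreme of the measured baseline with ρ of 0.5–0.7, less for softer loss, and none if loss is alike in both arms or unrelated to baseline. The adjusted analysis is valid under the usual missing-at-random assumption. If loss instead follows stable severity, the advantage on bias reverses, so neither analysis should be reported alone.

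**What to change.** In section 2.8, or in the analysis plan, make the main effect analysis baseline-adjusted. Either of these serves:
- ANCOVA of the post score on group and baseline score; or
- the equivalent SPSS MIXED model of baseline and post scores, with a common baseline mean, unstructured covariance and a group effect at post, using every randomised child with at least one assessment.

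Keep the planned group × time ANOVA as a sensitivity analysis and report both. State that the main model assumes missing at random, and that the change-score result can be the less biased one if loss follows a child's underlying severity. A disagreement between the two would then be read as a sign that loss matters.

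The cost is a few sentences of analysis text, settled before unblinding. It needs no new data, software or visits.

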### 2.5. Participants

In order to be eligible for inclusion in this project, participants must meet the following criteria: (1) having an ADHD clinical diagnosis; (2) no co-morbidities with other neurodevelopmental or psychiatric disorders; (3) aged between 8 and 16 years; (4) not suffering from pathologies that contraindicate the practice of exercise or limit the execution of the PA program; (5) and having authorisation from parents or legal guardians.

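### With two time points, the planned group × time ANOVA is a change-score t-test: valid, but usually less precise than ANCOVA on the baseline score, and below the stated 80% power if the pre-post correlation is under about 0.5

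*Protocol article*

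**What the plan says.** All references are to the protocol article.

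- **Section 2.1** sets two assessments, one before the 4-week intervention and one immediately after it, in a randomised parallel-group trial.
- **Section 2.8** names the model: a group × "time repeated measures ANOVA will be employed to analyse the impact of the intervention". Significance is judged on the within-group time effect and on the group × time interaction, and Cohen's d is given with a 95% confidence interval. No covariate is named.
- **Section 2.3** sizes the trial by "selecting the One-way ANOVA statistical test, that allows the comparison between the means of two independent groups", "assuming a large effect size f of 0.4". It arrives at "a total of 52 participants (being 26 subjects included in both experimental and control group"), which "will be sufficient in order to attain a minimum power of 80" per cent. No pre-post correlation enters this calculation.
- **Section 2.5** admits children "aged between 8 and 16 years". **Section 2.7** collects age, gender and medication once, before the programme.

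**The concern.** With two arms and two time points, the interaction F is the square of the t statistic comparing mean change between arms. A change score subtracts the whole baseline value, so it fixes the slope of post on baseline at 1. With equal variances at both times, the slope that minimises the variance is rho, which is below 1 for any imperfectly repeatable measure.

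Two things follow. The planned test uses the baseline inefficiently, although the baseline has been paid for. Any chance difference between the arms at baseline is also over-corrected, so the estimate drifts through regression to the mean. With 26 per arm such differences will not be small. The power in section 2.3 is also tied to a correlation that the protocol never states.

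**Working it through.** **Inputs from section 2.3:** alpha 0.05; f = 0.4, which for two equal arms is d = 2f = 0.8 SD of a single measurement; N = 52, 26 per arm. **Assumed:** rho, shown over a range; equal variances before and after; no dropout.

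**1. The plan's own figure.** One-way ANOVA with two groups: noncentrality λ = N·f² = 52 × 0.16 = 8.32, with 1 and 50 degrees of freedom. Power is 80.7%; N = 50 gives 79.1%. So 52 is the smallest even total for 80% and the figure reproduces. (The same section gives "considering a significance level of 0.05 (alpha), a 0.02 beta risk", which taken literally would need 104. That is a separate matter; 52 belongs to 80%.)

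**2. Identity of the tests.** In a simulated data set with two arms of 26 and two times, the interaction F was 12.2912 and the squared change-score t was 12.2912.

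**3. Residual variances, with the single-measurement SD as unit.**
- Change score: 2(1 − rho)
- ANCOVA: 1 − rho²
- Ratio of ANCOVA to change score: (1 − rho²) / [2(1 − rho)] = (1 + rho)/2

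Estimating the slope multiplies the ANCOVA variance by about 1 + 1/48 = 1.021 at N = 52. The ratio then passes 1 when (1 + rho)/2 × 49/48 = 1, that is rho = 96/49 − 1 = 0.96.

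**4. Power at d = 0.8, 26 per arm.** λ = 8.32 / [2(1 − rho)] with 50 df for the change score, and λ = 8.32 / (1 − rho²) with 49 df for ANCOVA. The slope cost is left out of the table.

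| rho | variance ratio (1 + rho)/2 | planned test | baseline-only ANCOVA |
|---|---|---|---|
| 0 | 0.50 | 51.6% | 80.7% |
| 0.3 | 0.65 | 66.7% | 84.2% |
| 0.4 | 0.70 | 73.3% | 87.0% |
| 0.5 | 0.75 | 80.7% | 90.4% |
| 0.6 | 0.80 | 88.5% | 94.2% |
| 0.7 | 0.85 | 95.5% | 97.7% |
| 0.8 | 0.90 | 99.4% | 99.7% |

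Dividing the ANCOVA λ by 1.021 lowers its power by less than one percentage point. At rho 0.5, for example, λ = 11.09/1.021 = 10.87 and power is 89.8%. Simulation (8,000 runs each) gave 80.5% vs 89.7% at rho 0.5, and 52.0% vs 79.8% at rho 0.

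**5. Link to section 2.3.** At rho 0.5 the change-score variance is 2 × 0.5 = 1, the same as a single measurement, so the planned test has exactly the design power of 80.7%. Below about 0.5 it falls under 80%. Baseline-only ANCOVA stays at about 80% or above for any rho from 0 upward.

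**6. Chance imbalance.** The standard error of a baseline mean difference is √(2/26) = 0.277 SD. Given a baseline difference Δ and a linear relation, the expected change-score estimate is off by (1 − rho)Δ. At rho 0.5 a one-standard-error imbalance shifts it by 0.5 × 0.277 = 0.14 SD, against a design effect of 0.8 SD. ANCOVA removes this shift.

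**The case against.** **The plan contains no error.** The interaction is a legitimate test in a randomised two-arm, two-time design, and it already uses the baseline. A reader might infer that the planned analysis is biased or invalid. It is not: over repeated randomisations the baseline difference averages zero, so the shift in step 6 does too. What remains is lost precision and sensitivity to the imbalance of this one randomisation. Nor is the model simply left to a fuller analysis plan, because section 2.8 names it.

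**ANCOVA is not always more precise.** A reader might infer that it can never do worse. That is a large-sample result. At N = 52 it can lose up to about 2% in variance, though only above rho of about 0.96.

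**The gain rests on an unstated correlation.** This stands. The programme lasts only 4 weeks, so high correlations cannot be excluded for some outcomes. At rho 0.8 the gain is 0.3 points. The 90% figure is conditional on rho 0.5 and is not a property of this trial.

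**Adding age, gender and medication may not help.** This also stands. Four slopes instead of one inflate the variance by about 1 + 4/45 = 1.09. If the three extra covariates explain nothing beyond baseline, power at rho 0.5 is about 87.8% rather than 90.4%, and the model loses to the change score above rho of about 2 × 45/49 − 1 = 0.84. The protocol does not say how strongly these variables relate to the outcomes, so a gain from them cannot be claimed.

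**The sociodemographic data are not barred from the model.** A reader might take "These data will only be considered at baseline" in section 2.7 as excluding them. In context it says when they are collected, in contrast to the measures taken twice.

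**Conclusion.** The point holds as an efficiency improvement that should be made, not as the correction of an error. The planned test equals a change-score t-test, which is valid but less precise than baseline-adjusted ANCOVA at any rho up to about 0.96. At rho 0.5 the variance ratio is 0.75, or 0.75 × 1.021 = 0.77 with the slope cost, so ANCOVA is worth about 30% more children (1/0.77 = 1.30). The gain is larger at lower correlations and negligible from about 0.8. The practical consequence for this protocol is that the 80% power in section 2.3 holds for the planned test only if rho is about 0.5 or more, whereas baseline ANCOVA keeps it at any non-negative rho.

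These sizes assume equal variances before and after, a linear relation, no dropout, and d = 0.8 in units of the single-measurement SD, as in the sample-size calculation. Rho is assumed throughout and may differ by outcome.

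**What to change.** In section 2.8, replace the group × time repeated-measures ANOVA, as the test of the intervention, with a linear model of the post-intervention score on group and the baseline score of the same outcome. Report the adjusted between-group difference with its 95% confidence interval as the treatment effect.

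Age, gender and medication may be added, but only if named in advance and expected to explain variance beyond baseline. With 52 children they otherwise cost precision.

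The cost is a change of text and one degree of freedom (49 instead of 50). Software, visits, measurements and sample size stay the same. The change should be fixed before anyone sees unblinded outcome data, so that it cannot be read as driven by results.

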Then, considering the PL influence on increased PA, PL may contribute to HRQoL improvement as well as to the quality and sustained attention of schoolchildren with ADHD. There is preliminary evidence that a PA program may improve the cognitive functions and functioning of children with ADHD [23], including attention issues [24,25]. Additionally, PA impacts the mental health of children with ADHD [26], as they show poorer PAL compared to typically developing children [26,27]. Therefore, this study aims to (1) assess the PL level in children and adolescents with ADHD in Spain; and (2) improve PL and consequently HRQoL and ADHD symptomatology, including quality and sustained attention, through a PL program based on PA improvement, motivation, education and healthy lifestyle habits.

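### No primary outcome is named and all outcomes are tested at an unadjusted 0.05, so the risk of a false-positive intervention effect exceeds 5%, by an amount that depends on how many scores are tested

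*Protocol article*

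**What the plan says.** Section 2.8 gives one analysis and one threshold for everything. A group × time "repeated measures ANOVA will be employed to analyse the impact of the intervention on the various dependent variables", and "Alpha significance level will be established at *p* ≤ 0.05". Two effects are judged for each variable: "Statistical significance will be determined for the within-group effect of time and the interaction group × time".

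Section 2.3 sizes the trial with a two-group one-way ANOVA, "assuming a large effect size f of 0.4", and arrives at 52 participants for at least 80% power. It does not say which outcome the effect size describes.

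The aims do not rank the outcomes either. The Introduction wants to "improve PL and consequently HRQoL and ADHD symptomatology, including quality and sustained attention", which puts physical literacy first. The Abstract and the Conclusions describe the effects under study as those on quality of life and ADHD symptoms.

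Section 2.7 numbers four constructs: physical literacy (CAPL-2), quality of life (CHU9D), ADHD symptoms (ADHDT) and attention (EMAV). Each instrument yields several scores. Of the CAPL-2 the section says "This assessment encompasses four distinct domains", alongside a 0–100 total. It opens with "PL and body composition will be evaluated through a variety of tools", but no body composition measure follows.

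**The concern.** A two-arm trial that tests many outcomes at 0.05 each, with none singled out, has no single hypothesis on which its 5% error rate holds. The more scores are tested, the likelier it is that an ineffective programme produces a significant interaction somewhere.

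This matters because the Abstract and the Conclusions make wider use of the programme in education depend on its effects being shown, and the article does not say on which outcome. The sample size shares the gap: 80% power at f = 0.4 describes one comparison, and the reader cannot tell which one.

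**Working it through.** **1. The plan's own figure.** Inputs from section 2.3: α = 0.05, f = 0.4, two groups, N = 52. The noncentrality is f²N = 0.16 × 52 = 8.32. With 1 and 50 degrees of freedom the power is 0.807. At N = 50 (noncentrality 8.00) it is 0.791. So 52 is correct for one two-group comparison. Section 2.3 prints a beta of 0.02, which does not agree with 80% power (1 − 0.80 = 0.20). That is a separate matter and does not enter below.

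**2. How many tests.** The article gives no count. From section 2.7:
- One score per numbered construct: 4.
- The same, with quality of attention and sustained attention kept apart: 5.
- Every score described: CAPL-2 total and four domains (5), CHU9D self-report and proxy (2), ADHDT total and three subscales (4), EMAV quality, omissions and errors (3). 5 + 2 + 4 + 3 = 14.

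Only the group × time test is counted, because it alone compares the arms. The within-group time test is left out.

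**3. Independent tests.** The chance of at least one p ≤ 0.05 when the programme has no effect on anything is 1 − 0.95^k:
- k = 4: 1 − 0.95^4 = 18.5%
- k = 5: 1 − 0.95^5 = 22.6%
- k = 14: 1 − 0.95^14 = 51.2%

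**4. Correlated tests.** The correlations are not in the article and are assumed. The model is k two-sided z tests with common correlation r, z_j = √r·g + √(1−r)·e_j, where g and e_j are independent standard normals (200,000 draws). The r = 0 column repeats step 3.

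| k | r = 0 | r = 0.3 | r = 0.5 | r = 0.7 |
|---|---|---|---|---|
| 4 | 18.5% | 17.4% | 15.6% | 12.9% |
| 5 | 22.6% | 20.9% | 18.2% | 14.7% |
| 14 | 51.2% | 44.1% | 34.9% | 24.8% |

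**5. Totals that contain their parts.** Fourteen independent scores are not possible if the CAPL-2 and ADHDT totals are sums of their parts. With both totals built that way:
- parts uncorrelated: 48%
- correlation 0.5 within and 0 between instruments: 42%
- 0.6 within and 0.3 between: 36%
- 0.7 within and 0.5 between: 29%

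**6. For comparison.** One primary outcome at 0.05 gives 5%. Bonferroni over 14 independent tests uses 0.05/14 = 0.0036 each and gives 1 − (1 − 0.0036)^14 = 4.9%.

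**The case against.** The other side has several fair arguments.

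- **The size does not follow from the stated rule.** A reader might infer that section 2.8 by itself implies 35–51%. It does not. That range needs 14 tests and a correlation between 0.5 and 0, neither of which is given, and its top cannot be reached once totals are built from parts. This stands, and the figures must be read as conditional.
- **Section 2.7 describes instruments, not a list of tested endpoints.** It does not say that the ADHDT subscales are analysed. It mentions a caregiver form of the CHU9D, yet says the measures are carried out by the participants. This stands, and four or five tests is a legitimate reading. Even four give 12.9–18.5% for r of 0.7 to 0.
- **No success rule is stated.** A reader might infer that one significant result on any score would be enough to declare the programme effective. The Abstract and the Conclusions say only what could follow if effects are shown. The probabilities above are therefore the chance of at least one false-positive interaction, not the error rate of a declared success rule.
- **The power statement is not empty.** N = 52 gives 80.7% for any single comparison at f = 0.4. This stands; what is missing is the named outcome.
- **A separate analysis plan or full protocol may deal with multiplicity.** It may, and silence on multiplicity alone would be no finding. But the article does state a threshold for all outcomes and does fix a sample size. A later adjustment would have to depart from the published rule.

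**Conclusion.** The point holds in conditional form. The article applies one unadjusted 0.05 level to all outcomes, designates none as primary and attaches its sample size to none. With no effect on anything, the chance of at least one significant group × time result is above the nominal 5% at every count and correlation examined.

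The size depends on assumptions. With four outcomes it is about 16–19% for a common correlation of 0.5 to 0. With all 14 described scores it is about 35–51% over the same range, with the upper end slightly overstated, and about 25% at a correlation of 0.7. The lack of a primary outcome and the shared threshold are certain; the percentages are scenarios.

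It might also be inferred that the CAPL-2 total must be the primary outcome. The documents do not settle this: the Introduction favours it, while the Abstract and the Conclusions stress quality of life and ADHD symptoms.

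**What to change.** Before unblinding:

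- **Section 2.8:** designate one primary outcome and test its group × time effect at two-sided 0.05. The CAPL-2 total is a natural candidate given the Introduction, but the choice is the authors'.
- **Section 2.3:** state that f = 0.4 refers to that outcome.
- **Key secondaries:** take one named score for each of the three remaining constructs and test them with Holm's procedure or in a fixed order. If 5% is to hold over primary and secondaries together, test them only after a significant primary result.
- **Everything else** (domains, subscales, other scores): report estimates with 95% confidence intervals and make no significance claims.
- **Section 2.7, separately:** reconcile the mention of body composition with the list of measures.

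The cost is about a paragraph in section 2.8 and a sentence in section 2.3, plus a check that the registration cited in section 2.2 agrees. Design and sample size do not change. The downside is that fewer outcomes can carry a significance claim.

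### The analysis section tests the effect of time at the same level as the group × time interaction and does not say which decides whether the programme worked, so a non-randomised change could be read as a programme effect

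*Protocol article*

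**What the plan says.** Section 2.8 names the model and its purpose: a group × "time repeated measures ANOVA will be employed to analyse the impact of the intervention on the various dependent variables". The inference rule follows: "Statistical significance will be determined for the within-group effect of time and the interaction group" × time. A single threshold covers both terms: "Alpha significance level will be established at" p ≤ 0.05. Cohen's d with a 95% confidence interval is promised, but the section does not say whether it is computed between or within groups. Nothing in it makes the interaction decisive.

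Three other places bear on the point:
- Section 2.1 describes a randomised parallel-group trial with a 4-week intervention, baseline assessment "followed by post-intervention evaluations immediately upon its completion".
- Section 2.3 sizes the trial on a comparison of two independent group means: "a total of 52 participants (being 26 subjects included in both experimental and control group").
- Section 2.7 repeats the same instruments at both time points. Before the first measurement, "participants will undergo a familiarization phase designed to acquaint them" with them.

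**The concern.** The trial is randomised so that the change in the programme arm can be set against the change in children who did not receive the programme. The interaction makes that comparison. The time effect does not. Pooled over arms, it asks whether children scored differently at the second visit, whatever their allocation. Taken within the experimental arm, it ignores the control group.

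Several outcomes can plausibly improve on a second attempt about four weeks later: the timed figure search (EMAV), the shuttle run, the agility circuit and the knowledge questionnaire. Regression to the mean can add to this where children enrol at a poor point. If both terms carry significance and neither is ranked, a significant pre-post change could be offered as evidence that the programme works even when both arms improved alike. Section 4 looks ahead to use by public administration and the private sector if the effects are demonstrated, so what counts as demonstration should be settled before data are seen.

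**Working it through.** **1. The plan's own sample size.** Section 2.3 gives f = 0.4, alpha 0.05 and power of at least 80%. For a one-way ANOVA with two groups, the noncentrality is λ = f² × N.
- N = 52: λ = 0.16 × 52 = 8.32, exact power 0.807.
- N = 50: λ = 0.16 × 50 = 8.00, exact power 0.791.

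So 26 per arm reproduces. It rests on beta = 0.20; the printed beta of 0.02 would need 52 per arm. The sizing is for a between-group comparison, not for a time effect.

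**2. Inputs for the illustration.**
- From the article: n = 26 per arm, two time points, alpha 0.05.
- Assumed, because the article gives neither: a gain g common to both arms (0.2 to 0.4 baseline SD) and a pre-post correlation r (0.5 to 0.7).
- Programme effect set to zero, and equal SD at both visits.

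**3. Formulas.** The SD of the change score is s = √(2(1 − r)) in baseline SD units: 1.000 at r = 0.5 and 0.775 at r = 0.7.
- Pooled time effect: noncentral t with parameter (g/s) × √52 on 50 df.
- Change in the experimental arm alone: parameter (g/s) × √26 on 25 df.
- Experimental arm significant and control arm not: p(1 − p), where p is the single-arm probability.
- Interaction: the shared gain cancels, so the parameter is 0 and the error rate is 5%.

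Worked case, r = 0.7 and g = 0.4: g/s = 0.4/0.775 = 0.516. The pooled parameter is 0.516 × 7.211 = 3.72, giving probability 0.955. The single-arm parameter is 0.516 × 5.099 = 2.63, giving 0.716. Then 0.716 × 0.284 = 0.203.

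**4. Results with no programme effect, per outcome.**

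| r | g (SD) | Pooled time effect significant | Experimental-arm change significant | Experimental significant, control not | Interaction significant |
|---|---|---|---|---|---|
| 0.5 | 0.2 | 0.293 | 0.165 | 0.138 | 0.05 |
| 0.5 | 0.4 | 0.807 | 0.500 | 0.250 | 0.05 |
| 0.7 | 0.2 | 0.447 | 0.245 | 0.185 | 0.05 |
| 0.7 | 0.4 | 0.955 | 0.716 | 0.203 | 0.05 |

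A 40,000-run simulation at r = 0.7 and g = 0.3 gave 0.784 for the time effect (0.782 by formula) and 0.049 for the interaction.

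**5. No shared gain at all.** If a significant result on either term counted as success, the error rate would still be about 1 − 0.95 × 0.95 = 0.0975 per outcome, roughly double the nominal 5%.

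**6. Precision of the adjusted contrast.** In units of SD², the residual variance is 2(1 − r) = 0.60 for a change score at r = 0.7, and 1 − r² = 0.51 after adjustment for baseline. Making the adjusted between-group difference the deciding analysis therefore loses no precision.

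**The case against.** The best defence is that the valid test is already in the plan. With two time points, the group × time interaction is the between-group comparison of change. It holds its 5% error rate whatever gain the arms share, and the time term is routine output of the same ANOVA. This stands, and it means that the planned model is sound.

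A reader might infer that retest gains *would* be reported as programme effects, or that the investigators intend to contrast a significant change in one arm with a non-significant change in the other. The document supports neither. Section 2.8 does not say that a time effect will be read as a programme effect, and it plans no comparison of p-values between arms. The phrase about time may mean only the model's within-subject factor. The column for that contrast in the table shows what such a misuse would cost and is not a forecast.

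The practice argument also has limits. The familiarisation phase in section 2.7 precedes baseline and should reduce early practice gain. Maturation over four weeks is probably small. Step counts, CHU9D quality of life and ADHDT symptom ratings are not skill tests. But familiarisation does not turn a within-group change into a treatment contrast, and it does nothing about regression to the mean.

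Finally, a condensed article may leave detail to a separate analysis plan. That excuses omissions. Here the article itself states which terms carry significance and gives the non-randomised one equal standing.

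**Conclusion.** The concern holds as a defect in the stated inference rule: two effects share one threshold, only one of them is a randomised comparison, and the text does not say which decides. The plan permits a time effect to support a claim of effectiveness; it does not commit to that reading.

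If the time effect were allowed to count, the chance of a false claim per outcome would be 29% to 95% for the pooled effect and 17% to 72% for the experimental arm alone, against 5% for the interaction. These ranges rest on an assumed shared gain of 0.2 to 0.4 SD and a correlation of 0.5 to 0.7, with 26 per arm and no programme effect. Smaller gains give smaller figures. That only the interaction is a randomised comparison depends on none of these assumptions. Because the valid test is already planned, this is a should-fix.

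**What to change.** Replace the sentence on statistical significance in section 2.8 with wording such as: *The intervention effect is the between-group difference at post-intervention, adjusted for baseline, with its 95% CI; this is the only basis for effectiveness claims. Time effects and within-group changes are descriptive and are not compared between arms by p-value. Cohen's d is the between-group d.*

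If the investigators prefer to keep the repeated measures ANOVA, naming the group × time interaction with its 95% CI as the sole test of the programme serves the same purpose. The adjusted difference is at least as precise and uses the baseline scores already collected.

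The cost is a few lines of text. Sample size, visits, instruments and staffing are unchanged.
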